# PATHWEIGH, pragmatic weight management in adult patients in primary care in Colorado, USA: study protocol for a stepped wedge cluster randomized trial

**DOI:** 10.1186/s13063-021-05954-7

**Published:** 2022-01-10

**Keywords:** Cluster randomized trial, Mixed methods, Pragmatic trial, PRISM, RE-AIM, Stepped wedge, Weight loss

## Abstract

**Background:**

Despite the overwhelming prevalence and health implications of obesity, it is rarely adequately addressed in a health care setting. PATHWEIGH is a pragmatic approach to weight management that uses tools built into the electronic medical record to overcome barriers and guide care. Implementation strategies are employed to facilitate adoption and use of the PATHWEIGH tools and processes. The current study will compare the effectiveness of PATHWEIGH versus standard of care (SOC) on patient weight loss in primary care and explore factors for its successful implementation.

**Methods:**

A stepped wedge cluster randomized trial design will be used within an effectiveness-implementation hybrid study. Adult patient weight loss and weight loss maintenance will be compared in PATHWEIGH versus SOC in 57 family and internal medicine clinics in a large health system in Colorado, USA. Effectiveness will be evaluated using generalized linear mixed models to determine statistical differences in weight loss and weight loss maintenance at 6, 12, and 18 months. Patient-, provider-, and clinic-level predictors will be identified using mediator and moderator analyses. Conceptually guided by the Practical, Robust, Implementation and Sustainability Model (PRISM), a mixed methods approach including quantitative (practice surveys, use tracking) and qualitative (interviews, observations) data collection will be used to determine factors impeding and facilitating adoption, implementation, and maintenance of PATHWEIGH and evaluate specified implementation strategies. A cost analysis of the practice and system costs and resources required by PATHWEIGH relative to the reimbursement collected will be performed.

**Discussion:**

The effectiveness and implementation of PATHWEIGH, and their interrelatedness, for patient weight loss are collectively the focus of the current trial. Findings from this study are expected to serve as a blueprint for available and effective weight management in primary care medical practice.

**Trial registration:**

ClinicalTrials.govNCT04678752. Registered on December 21, 2020.

**Supplementary Information:**

The online version contains supplementary material available at 10.1186/s13063-021-05954-7.

## Background

In the USA, obesity prevalence continues to increase. In 2019, the Centers for Disease Control and Prevention (CDC) estimated that 70% of US adults were considered overweight and 42% had obesity [1]. Obesity is a well-established risk factor for numerous diseases, including diabetes, cardiovascular disease, cancer, immobility, mental health issues, as well as all-cause mortality [2]. Obesity is also a strong and independent risk factor for poor outcomes due to COVID-19 [3]. In 2018, direct and indirect costs associated with obesity in the USA reached $1.7 T [4]. Importantly, obesity is being increasingly recognized not only as a risk factor for disease, but a disease unto itself [2]. Despite this, obesity is rarely addressed in a healthcare setting. Only ~ 50% of people with a BMI of 50 kg/m^2^ (considered morbid or extreme obesity) have a documented diagnosis of obesity [5] and < 1% of people with any degree of overweight or obesity are offered anything other than lifestyle advice [6].

Reasons behind the lack of weight management prioritization in clinical settings are extensive and complex. Health care providers cite lack of time, education, and resources, as well as competing issues, as the leading reasons why obesity is not prioritized [7–9], but poor reimbursement and lack of effective tools are also widely cited [7, 8]. Further, lack of data on long-term effectiveness of weight loss treatments leads to uncertainty and learned helplessness among both health care providers and patients. Eighty-two percent of people with obesity believe they are responsible for their weight; a number highly corroborated by health care providers, enhancing shame and hesitancy to seek help [7]. While these are only a few of the reasons why weight is rarely addressed, increasing evidence suggests barriers can be overcome by intentionally employing long-term evidence-based strategies. Importantly, such strategies must be employed where patients access care, most notably in primary care.

Primary care is undergoing rapid transformation with a shift toward population-based approaches that prioritize preventive care. Initiatives such as pay for performance, the Patient-Centered Medical Home [10], and efforts associated with the Affordable Care Act [11] have brought a host of structures, tools, and processes not previously available, creating new opportunities to engage patients in efficacious programs. Many practices now have electronic medical records (EMRs), patient registries, and a team approach to care that may include expanded care visits with care managers, dietitians, and social workers or psychologists [12, 13]. Increasingly, value-based payment models incentivize practices to identify patients at high risk for complications of chronic conditions and to mitigate these risks. Many of these chronic conditions can be improved or alleviated by reducing excess weight.

Importantly, patient demand is high for weight management in primary care*.* A study by Sherson et al. [14] reported that the majority of patients want to discuss weight loss with their physicians. Specifically, patients value physician direction with their diet, physical activity, and goal setting [15]. In addition, recent years have ushered in numerous and diverse options for weight management that extend significantly beyond lifestyle advice. Medications for weight loss are being more extensively studied and demonstrating improved outcomes [16–19]. Bariatric surgery provides a possible option to address weight and reverse potentially life-threatening conditions such as heart disease and diabetes in both adolescents and adults [20–23]. Intensive behavioral therapy (IBT) for obesity is now a covered benefit under Medicare [24]. Together, primary care practice transformation, reimbursement for obesity care, and better therapies for weight management suggest new and pragmatic approaches can emerge.

In the Fall of 2020, the National Institutes of Health (NIH) National Institute of Diabetes and Digestive and Kidney Diseases (NIDDK) funded “PATHWEIGH: pragmatic weight management in primary care” (1R18DK127003). The aim of PATHWEIGH is to create the blueprint for pragmatic, scalable, and sustainable weight management in primary care using existing resources. To achieve this aim, this study will deploy an effectiveness-implementation hybrid type 1 [25] stepped wedge cluster randomized trial design [26] in 57 health-system owned family medicine and general internal medicine clinics that span diverse settings, patient populations, and community contexts in Colorado.

## Aims and hypotheses

The specific aims of the current research are to:
Compare the effectiveness of PATHWEIGH versus standard of care (SOC) on weight loss and weight loss maintenance.Identify patient, provider, and clinic-level predictors that are associated with weight loss and weight loss maintenance.Describe factors associated with practice adoption, implementation, and maintenance of PATHWEIGH.

We hypothesize that PATHWEIGH will lead to greater weight loss at 6 months (primary) and greater weight loss maintenance at 12 and 18 months (secondary) compared to SOC [Hypothesis I]. Key patient, clinician, and clinic characteristics will mediate and moderate patient weight loss and weight loss maintenance [Hypothesis II]. Effective implementation will be vital to anticipated implementation and clinical outcomes [Hypothesis III].

## Methods

The study methods are described in compliance with the SPIRIT statement [27] and the Consolidated Standards of Reporting Trials (CONSORT) extension for stepped wedge cluster randomized trials [28] to ensure appropriate reporting of the study protocol and completed trial. The SPIRIT checklist is provided in the Additional file.

### Study setting

This study will be conducted in 57 family medicine and general internal medicine clinics within a large, multi-specialty health care system in Colorado (Fig. 1). One primary care clinic was excluded as it was a pilot test site [29]. These practices are comprised of approximately 400 clinician full-time equivalents (physician, nurse practitioner, physician assistant) caring for nearly 500,000 patients in diverse geographic and socioeconomic contexts. All practices have the following resources for the implementation of obesity management: access and full use of the Epic EMR, practice quality improvement facilitators, standardized workflows for medical assistants, funds for site innovation, inter-connectedness to the system at large, and regular training opportunities. Primary care leadership has unanimously offered their support for this project.

**Fig. 1 Fig1:**
[figure not shown]
Location of participating Colorado and Wyoming clinics. Image created using Google Map data 2022

### Design and randomization

We will use a type 1 hybrid effectiveness-implementation stepped wedge cluster randomized design to assess both patient-level clinical and practice-level implementation outcomes [25, 26]. The intervention will be implemented sequentially in the 57 participating clinics in three steps over a 4-year period (Fig. 2). All sites will start in the control condition of SOC for weight management. Every year, one sequence of clinics will transition to the intervention condition after which the use of PATHWEIGH will be encouraged for all weight-prioritized visits and corresponding PATHWEIGH implementation strategies will be provided. Clinics were randomly assigned by the study statistician to each sequence using covariate constrained randomization [30] to achieve balance on clinic type (academic, affiliate, non-academic), clinic location (urban/suburban vs. rural), provider type (family medicine (FM), general internal medicine (GIM), or both), annual number of patient visits, and patient insurance status (percentage Medicaid) (Table 1). A stepped wedge extension for this procedure was used to account for the proportion of the study period that each of the sites spend in the control and intervention periods [30]. For additional details about the randomization procedure see Additional file.

**Fig. 2 Fig2:**
[figure not shown]
Study diagram for the PATHWEIGH study, a stepped-wedge cluster hybrid type 1 randomized controlled trial design

**Table 1 Tab1:** Characteristics of participating practices and patients by randomization sequence

Site characteristic	Sequence 1 (20 clinics)	Sequence 2 (18 clinics)	Sequence 3 (19 clinics)
**Type,** *n*			
Academic	1	1	2
Affiliate	4	2	2
Non-academic	15	15	15
**Location,** *n*			
Urban	17	16	16
Rural	3	2	3
**Specialty,** *n*			
Family Medicine only (FM)	10	9	11
General Internal Medicine only (GIM)	6	6	4
Mixed FM/GIM	4	3	4
**Number of patients visits in 2019,** median (IQR)	10,589 (6059–22,233)	13,579 (7666–20,035)	9815 (3552–29,910)
**Percentage Medicaid,** median (IQR)	3.5 (2.0–5.0)	5.0 (3.0–7.0)	2.5 (1.8–7.0)

### Participant eligibility criteria

Patients eligible for this analysis must (1) be aged 18 years or older, (2) be overweight (BMI ≥25 kg/m^2^) at initial visit, and (3) have had at least one weight-prioritized visit in a participating clinic. Exclusion criteria in the original protocol include limited cognitive ability, have a non-home residence, or have less than 1-year life expectancy. Ultimately, these were not applied due to the inability to obtain the necessary fields in the data extraction; however, the number of individuals that would be excluded based on these criteria is expected to be minimal and balanced across the study arms. Weight-prioritized visits are defined as the chief complaint or reason for the visit being at least one of the following: (1) “overweight,” “obesity,” or “weight,” (2) ICD-10-CM codes for billing E66–E.66.9, Z68.25–45, (3) use of the “obesity brief HPI” Epic flowsheet, or (4) the PATHWEIGH patient questionnaire.

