### Sample size

A conservative sample size estimate is 6840 total patients (120 patients per clinic from 57 clinics) that assume a minimum of 30 eligible patients per clinic per year based on the smallest clinic. We present the power calculations assuming an intraclass correlation coefficient (ICC) between 0.02 and 0.05. With this design, we will have 80% power (alpha=0.05, two-sided) to detect a standardized effect size of 0.118 (ICC=0.02) to 0.121 (ICC=0.05). For our primary effectiveness outcomes, we estimate a standard deviation (SD) of 10.1 percentage points for percentage change in weight using our pilot study, and a similar SD estimate of 10.7 for absolute (kg) change in weight. Thus, with 80% power we can detect a mean difference in weight change of 1.19 (ICC=0.02) to 1.22 (ICC=0.05) percentage points between the control and intervention conditions, and a mean difference in absolute weight change of 1.26 kg (ICC=0.02) to 1.29 kg (ICC=0.05).

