**Fig. 4 Fig4:**
[figure not shown]
PATHWEIGH clinic flow

**Table 2 Tab2:** Key components of PATHWEIGH and PATHWEIGH implementation strategies

***PATHWEIGH is a weight management care path built into Epic.*** It includes: • Weight-prioritized visit type: Defines the scope of the visit for the patient and provider. • Time-efficient documentation and data capture: Patient questionnaire completed prior to the visit captures history around weight gain and barriers to weight loss that can guide the patient-clinician conversation and treatment plan. • Clinical decision support: SmartSet in Epic suggests weight loss approach(es) based on patient BMI and preferences according to the Obesity Society guidelines [32]. • Tracking: Displays progress with weight loss and weight loss maintenance during patient visits to guide the patient-clinician conversation and evolving treatment plan over time. • Diagnosis and billing: Tool in Epic automatically adds the diagnosis of overweight (for BMI 25-29.9 kg/m^2^) or obesity (for BMI> 30 kg/m^2^) and links the most common weight-related co-morbidities (according to the Center for Medicare and Medicaid Services) to ensure adequate provider reimbursement.	
***PATHWEIGH implementation strategies*** include: • Practice facilitation: Practice facilitators drive implementation efforts by working with practice-selected Practice Champions, engaging leadership in goal setting and monitoring along system and practice goals, and utilizing quality improvement techniques for supporting adoption, implementation, and management of PATHWEIGH. • Clinician education: Online e-learning module on evidence-based weight management treatment which includes 2 credits of continuing medical education. • Consultation support: built-in to Epic consultation support for clinicians by request; built-in to Epic availability of UpToDate, a subscription-based clinical reference.	

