#### Analysis

A generalized linear mixed modeling strategy will be employed to account for multiple levels of correlation (i.e., between patients within practices and between measurements on a single patient over time) [44]. This approach allows for the most efficient use of data if any follow-up measurements are missing for some subjects. We will follow an intention-to-treat approach for our primary analysis, i.e., patients will be analyzed according to their clinic’s intervention condition (PATHWEIGH vs. SOC) at the time of the patient’s index visit. An index visit will be defined as the patient’s first weight-prioritized visit in an intervention condition. Follow-up visits at which weight is recorded will be associated with the intervention status of the patient’s preceding index visit.

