For the primary analysis, although the parameter of interest is weight change at 6 months, weight collected from baseline to approximately 9 months post-baseline for the individual patient will be included in the primary analysis because patients may not have visits with recorded weight within the 6-month time frame. The mixed model will include random intercepts for patient, provider, and clinic, along with fixed effects for time and intervention condition. The time effects are two-fold: (i) calendar time, divided into four 1-year periods and included as a categorical variable to flexibly model its effect on the outcome and account for temporal trends, and (ii) individual patient time, included as a continuous variable (i.e., time from baseline) to accommodate varying visit times determined by each patient’s visit schedule. The intervention condition variable will be a binary indicator that is equal to zero if the patient’s index visit occurs at a clinic when it is in the control condition and becomes equal to 1 when the patient has an index visit at a clinic after it has crossed into the intervention condition. Patient-, provider-, and practice-level covariates will be included in models if deemed to be potential confounders in univariate models. An additional fixed effect for the interaction between patient time and intervention condition will be used to estimate the parameters of primary interest, i.e., the difference in change in outcomes over time between the intervention and control conditions. The primary analysis will test the null hypothesis that the interaction effect coefficient is equal to zero to determine whether there is a significant difference in weight change between the PATHWEIGH and SOC conditions. Using the model, we will report the mean weight change in the control and intervention groups and their difference at 6 months, with corresponding 95% confidence intervals and *p* values.

To examine the secondary binary outcomes of weight maintenance (defined as < 10% weight gain at 12 and 18 months), we will use generalized linear mixed models. Since this analysis will involve a single outcome per patient, the model will only include a random intercept for provider and clinic. The test of intervention effectiveness will be captured by the fixed effect term for the intervention condition.

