The primary analysis is expected to provide a conservative estimate of the treatment effect, and we propose the following secondary analyses to assess the treatment effect in alternative cohorts. We will perform a per-protocol analysis that uses the described models to compare those that received PATHWEIGH to those with a SOC weight-prioritized visit. This analysis will provide a better estimate of the efficacy of the intervention by including only those in the PATHWEIGH condition that were considered to satisfy the criteria for receiving the intervention as assessed by the provider’s use of at least one of a weight prioritized visit “type”, the patient weight management questionnaire, and/or the weight management SmartSet. Additionally, we will perform an analysis using all those that are eligible for PATHWEIGH based on the criteria of age and BMI, regardless of whether they had a weight-prioritized visit. This analysis will allow us to account for the potential selection bias induced by the implementation of PATHWEIGH potentially increasing the number of weight-prioritized visits and thus increasing the enrollment of patients in the intervention period that differ systematically from those in the control period.

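### Index visits are defined differently under PATHWEIGH and SOC, and SOC patients can be re-indexed after crossover, so the primary estimate is not assured to be conservative

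*Protocol article*

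**What the plan says.** **Entry.** Under Participant eligibility criteria, a visit is weight-prioritized if it meets any of four criteria: a weight-related chief complaint, listed ICD-10 codes, the Obesity brief HPI flowsheet, or the fourth route, "Epic flowsheet, or (4) the PATHWEIGH patient questionnaire". The section on current standard of care states that SOC clinics have no access to the PATHWEIGH tools. Table 2 says of the PATHWEIGH package: "Tool in Epic automatically adds the diagnosis of overweight" (or obesity). The intervention sections add that patients are encouraged to book weight visits, and that front-desk placards may tell them they can.

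**Follow-up.** The Aim 1 analysis is labelled intention-to-treat, by the clinic's condition at the index visit. The index visit is the patient's first weight-prioritized visit in a condition. "Follow-up visits at which weight is recorded will be associated with the intervention status of the" index visit that came before. The condition indicator becomes 1 once the patient has an index visit after the clinic has crossed over.

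**Claims built on this.** "The primary analysis is expected to provide a conservative estimate of the treatment effect". For the 12- and 18-month maintenance outcomes: "Since this analysis will involve a single outcome per patient, the model will only include a random intercept for provider and clinic".

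The same section concedes that PATHWEIGH may bring in patients who differ systematically from control-period patients. It plans a secondary analysis of everyone eligible by age and BMI, with or without a weight-prioritized visit.

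**The concern.** Clinics are randomized, but patients are admitted afterwards by a rule that the intervention itself alters. Assigning each patient to the clinic's condition at index follows the randomization, yet it does not make the patients admitted under the two conditions comparable. A visit that qualifies only through the questionnaire has no SOC counterpart.

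Follow-up is also asymmetric. A SOC episode ends when the patient comes back for a weight visit after crossover; a PATHWEIGH episode cannot end that way, because clinics do not cross back. SOC weights recorded after crossover therefore come from patients who did not return for a weight visit, in clinics already using PATHWEIGH.

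At stake are the meaning of the primary 6-month contrast, the assurance given to readers that any error is towards the null, and the standard errors of the maintenance models if the same patient appears twice.

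**Working it through.** **1. The plan's own yardstick.** Inputs from Sample size, Design and randomization, and Table 1: "6840 total patients (120 patients per clinic from 57 clinics"; the plan says these figures "assume a minimum of 30 eligible patients per clinic per year based on the smallest clinic"; four 1-year periods; sequences of 20, 18 and 19 clinics; SD 10.7 kg.
- Patients: 57 × 30 × 4 = 6840, as stated.
- Detectable effect = (z0.975 + z0.80) × SE, from a stepped-wedge model with fixed period effects and a random clinic intercept: 0.117 (ICC 0.02) and 0.120 (ICC 0.05). With t quantiles on 167 df it is 0.118 and 0.121. The plan states "we will have 80% power (alpha=0.05, two-sided) to detect a standardized effect size of 0.118 (ICC=0.02) to 0.121 (ICC=0.05". This reproduces.
- In kg: 0.118 × 10.7 = 1.26; 0.121 × 10.7 = 1.29. The SE at ICC 0.02 is 0.447 kg.

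The sample size is not in question. It takes patients to be exchangeable across conditions, which is the assumption at issue.

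**2. The four entry routes by condition.**
- Chief complaint: available in both; more visits are invited under PATHWEIGH.
- ICD-10 codes: available in both; under PATHWEIGH a tool can add them.
- Obesity brief HPI: available to all Epic users.
- PATHWEIGH questionnaire: PATHWEIGH only.

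**3. How much SOC follow-up lies after crossover.** Assume even enrolment over control time and control periods of 1, 2 and 3 years. Control clinic-years = 20×1 + 18×2 + 19×3 = 113. The share of SOC index patients whose outcome date falls after their clinic's crossover is:
- 6 months: 57 × 0.5 / 113 = 25.2%
- 9 months (end of the primary window): 57 × 0.75 / 113 = 37.8%
- 12 months: 57 × 1 / 113 = 50.4%
- 18 months: (20×1 + 18×1.5 + 19×1.5) / 113 = 75.5 / 113 = 66.8%

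Sequence 1 has one control year, so all 20 of its control clinic-years fall in the exposed part at both 12 and 18 months.

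**4. Entry bias, as a range only.** Let f be the share of intervention index patients admitted only because of the intervention, by any route, and D their difference from other index patients in usual 6-month weight loss. Bias = f × D. The protocol gives neither quantity, so these values are assumptions. With no true effect and SE 0.447 kg, the false-positive rate is Φ(b/SE − 1.96) + Φ(−b/SE − 1.96):
- f = 0.1, D = 1 kg: b = 0.10 kg, rate 5.6%
- f = 0.2, D = 2 kg: b = 0.40 kg, rate 14.6%
- f = 0.3, D = 2 kg: b = 0.60 kg (48% of 1.26), rate 26.9%

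With D of the opposite sign, the bias reverses.

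**5. Does dilution guarantee conservatism?** If a share u of intervention patients is unexposed and the true effect is Δ, the estimate is roughly (1 − u)Δ + fD. It exceeds Δ when D > uΔ/f. With Δ = 1.26 kg:
- u = 0.2, f = 0.3: D > 0.2 × 1.26 / 0.3 = 0.84 kg
- u = 0.4, f = 0.2: D > 0.4 × 1.26 / 0.2 = 2.52 kg

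Either order is possible, so dilution alone does not settle the direction.

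**6. One outcome per patient?** Take a sequence 3 patient indexed in the first half of year 1. The SOC 18-month date falls by month 24, before crossover at month 36. If re-indexed in year 4 (months 36 to 48), the second 12-month date is months 48 to 60 and the second 18-month date months 54 to 66. Extraction from 17 March 2020 to 17 September 2025 spans 66 months (taking the four years to start on the first date). Such a patient can contribute twice to each maintenance model.

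**The case against.** Entry selection is disclosed, not overlooked: the protocol names it, plans the all-eligible analysis, and will report counts of eligible and weight-prioritized patients in an expanded CONSORT diagram. The questionnaire is requested once a weight visit has been scheduled, so the fourth criterion should overlap heavily with the first. The diagnosis function belongs to optional tools and does not code every patient with a qualifying BMI. Classifying by condition at index is a usual stepped-wedge choice, and the primary model already has a patient random intercept. The claim of conservatism is worded as an expectation and most naturally refers to dilution from non-use. A single outcome may simply mean one value per time point rather than repeated weights.

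Most of this stands and limits the point. It does not make the trigger list common to both conditions, and the all-eligible analysis leaves the primary estimate as it is. Nor does dilution fix the sign of the net bias. One value per time point is still one per index episode, and a patient can have two episodes.

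A reader might infer that the primary analysis favours PATHWEIGH. The documents do not support that: D could have either sign, and SOC follow-up in clinics already using PATHWEIGH would be expected to dilute the effect. A reader might also take the 25%, 50% and 67% shares as the size of the bias. They are not: re-indexing also needs a new weight-prioritized visit, whose frequency is not given, and about 75% of SOC index patients reach 6 months before crossover.

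**Conclusion.** The concern holds in a limited form. The entry definition differs by condition, and the re-indexing rule makes post-crossover SOC follow-up depend on not returning for a weight visit. The supportable conclusion is that the primary estimate is not assured to be conservative; size and direction of the bias are unknown. The exposure figures rest on even enrolment; if first SOC visits cluster early in the control period, they are lower. The f and D values are illustrative and have no anchor in the protocol. Separately, the premise of a single outcome per patient in the maintenance models is wrong under the protocol's own index rule, so those models omit within-patient correlation. The stated sample size is unaffected. These are rules fixed in the article, and they should be amended.

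**What to change.** (a) For the primary analysis, use only triggers available in both conditions: a visit that qualifies solely through the PATHWEIGH questionnaire is not an index visit. Keep visits with a qualifying diagnosis code whatever its source. Removing tool-placed codes would selectively drop visits that a SOC clinician might have coded by hand. Interpret the primary result alongside the all-eligible analysis, because common triggers do not remove invited visits.

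(b) Add a sensitivity analysis of the 6-month primary outcome that censors SOC follow-up at the clinic's crossover date. Do not make this the main rule at 12 and 18 months, where sequence 1 would lose essentially all its control outcomes.

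(c) Replace the statement on conservatism with one saying that non-use dilutes the effect, while selective entry may bias it either way. In the 12- and 18-month maintenance models, add a patient random effect or patient-level clustering, or restrict to one index episode per patient.

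Cost: wording and code, with no new data collection; slightly fewer intervention index visits and slightly wider intervals in the secondary models.
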